#### EMA

During the intervention period, all employees will also be asked to participate in the EMA. EMA is a method for self-monitoring through the collection of self-reports on indices of behavior, cognition, or emotions in near real time in the daily lives of the participants, often through digital devices [42-44]. The smartphone-based questionnaire app allows us to digitally collect daily life momentary assessments of changes in employees’ levels of fatigue and recovery behavior, in relation to momentary context and activity. As such, it provides insight into the short-term, within-person mechanisms linking fatigue and recovery with short-term intervention effects. Event-contingent data collection protocols will be used, indicating that data entry takes place when a predefined event occurs [45,46]. The predefined event in this study is the formal work break. Participants will be asked to fill the data in the EMA app for a period of 14 consecutive days (1) directly before taking a work break, (2) directly after taking a work break, and (3) directly after the end of their shift. Each measurement moment will take about 1-2 minutes. In alignment with organizational management, we chose a period of 14 days to ensure enough day-level data points (despite rotating shift schedules and possible dropouts) without overburdening the participants. The use of the intervention, however, can continue after data has been collected.

Table 1 shows the variables that will be measured. The information provided will give insight into the effectiveness of the different recovery strategies (eg, relaxation and activation) and the influence of work break control, shift types, and personal characteristics (eg, age, chronotype, job position) on recovery outcomes. The start of the 14-day EMA period will be communicated through (1) the app via prompts, (2) the manager of the specific unit, and (3) through communication at the workplace (eg, posters, newsletters).

**Table 1 table1:** Variables retrieved through EMA.

Variable	Items	Questionnaire	Before break	After break	After shift
Shift type	1	What shift are you working today?	✓		
Sleepiness	1	Karolinska Sleepiness Scale [47]: scored on a scale from 1 (extremely alert) to 10 (very sleepy, difficulty in staying awake)	✓	✓	✓
Stress	1	Self-developed: “How do you currently feel?” scored on a visual analog scale (ranging from “stressed” to “relaxed”)	✓	✓	✓
Need for work break	1	Self-developed: “To what extent are you in need of a work break right now?” scored on a scale ranging from 1 (not at all) to 10 (to a great extent)	✓		
Detachment from work	3	Based on de Jonge et al [33]: scored on a scale ranging from 1 (completely disagree) to 10 (completely agree)		✓	
Recovery activities	2	Self-developed: “During this work break, I spent my time mainly…”. 1 item scored with 3 answering categories: 1 (on activation activities such as walking, exercising, playing a game); 2 (on relaxation activities such as sitting, reading, listening to music, and power nap); and 3 ((other activities (please specify)) 1 item scored with 2 answering categories: 1 (alone) and 2 (with others).		✓	
Control	1	Self-developed: “I was able to decide for myself how to spend my time during this work break” scored on a scale ranging from 1 (completely disagree) to 10 (completely agree)		✓	
Work break satisfaction	1	Self-developed: “I am satisfied with the way I spend my time during this work break” scored on a scale ranging from 1 (completely disagree) to 10 (completely agree)		✓	
Level of recovery	1	Based on Demerouti et al [20]: “At this moment, I feel sufficiently recovered” scored on a scale ranging from 1 (completely disagree) to 10 (completely agree)		✓	
Productivity	1	Self-developed: “To what extent were you able to work productively during this shift?” scored on a scale ranging from 1 (not at all) to 10 (a great extent)			✓
Safety	1	Self-developed: “To what extent were you able to work safely during this shift?” scored on a scale ranging from 1 (not at all) to 10 (a great extent)			✓

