### Study Objectives

Studies have shown that the experience of psychological detachment from work is an effective ingredient for an intervention aimed at enhancing recovery during work [13-15]. This experience may be evoked through either relaxing or activating recovery activities as long as employees have a sense of control with regard to choosing their recovery activities. Nevertheless, the optimal intervention for enhancing recovery during the work of shift workers has not been elucidated in practical settings. Therefore, the main objective of this study is to develop, implement, and evaluate an intervention aimed at improving recovery during work and thereby reduce the negative short-term effects of shift work. Not only the content but also the intervention development and implementation process can affect the outcomes of the respective intervention [25,26]. The evaluation will therefore focus on the effects of the intervention as well as the process of intervention development and implementation. The corresponding research questions of this study are as follows:

What is an optimal intervention to enhance recovery during work for shift workers in practice?To what extent is this intervention effective in enhancing recovery during work and in reducing the negative short-term effects of shift work?What are the hindering and facilitating factors for the development and implementation of the intervention?

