#### Phase 1: Needs Assessment

In phase 1, we aim to assess the initial design specifications and the user requirements for the intervention to meet the needs of the target group. The basic needs and requirements of the intervention will be determined in close consultation with the target group. To this end, we will apply a user-centered design approach. First, the researchers will observe the workplace of the participating departmental units and conduct semistructured interviews with the employees and departmental and unit managers to gain insight into the characteristics of the target group, their specific work activities, and their current recovery practices. Second, the employees from the participating units (ie, intervention groups) will be invited to participate in 2 successive so-called user sessions that are led by the researchers. In these sessions, evidence-based and theory-based recovery practices (ie, psychological detachment, relaxation and activating recovery activities) will be presented and discussed. Specifically, employees will be asked for their recovery needs (eg, preferred work break activities) in context to specific work shifts (ie, morning, evening, night). In addition, they will be asked for ideas on how to incorporate new recovery practices into their current work and recovery routines. For reasons of feasibility, the focus will be on their formal work breaks. These ideas will then be rated on desirability by all employees. A voting procedure will be used to reach consensus. Phase 1 will result in an overview of the general intervention requirements.

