### Statistical Analysis

First, intervention results will be analyzed by performing mixed model repeated measures analyses (multivariate analysis of variance; time*group interaction) on longitudinal survey data with the outcome measures at follow-up (T0-T1, T1-T2, and T0-T2 comparisons) as the dependent variables. Furthermore, the effectiveness of the intervention will be analyzed by applying multilevel analyses on data collected within the EMA study (before break-after break and before break-after shift comparisons). Data will be collected and analyzed at 3 levels: (1) day level, (2) employee level, and (3) work unit level. Dropouts will be documented and included in the data analysis to the point of dropout. Potential confounders or effect modifiers (eg, age, gender, chronotype) will be compared between the intervention and the waiting list control group by *t* tests for independent samples and chi-square tests. For all analyses, a two-tailed significance level of *P*<.05 will be applied. The multilevel analyses will be conducted using R and the mixed model repeated measures analyses will be performed using SPSS software (IBM Corp, Version 25.0). A detailed analysis plan will be developed prior to finalization of the dataset.

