### Study Strengths

The design of this study has several strengths. First, by making use of the PAR approach, stakeholders at all levels of the company are involved. This bottom-up involvement of the stakeholders will contribute to the commitment to the proposed interventions, which will likely translate into better overall intervention adherence and compliance. Moreover, it allows the target group to participate in the development and implementation of the intervention. This approach will stimulate problem ownership and commitment at all levels of the organization and has the potential to contribute to organizational sustainability [29], for which the interventions are more likely to have the proposed impact [28]. Another strength of the study design is that the timeline for the experimental unit allows us to compare the short-term intervention effects (T1) with the long-term effects (T2). In addition, the intervention development is conducted in a similar way in both the departments, but the eventual workplace interventions can differ. As a consequence, we can compare different solutions on similar proposed outcomes, further contributing to both theory and evidence-based practice [54]. In addition, to determine the effects of the workplace intervention, we use a rather unique data triangulation. Next to group-level outcome measurements with a web-based questionnaire, EMA measurements are used to gain insight into the working mechanisms of the intervention and to determine the influence of the type of recovery strategy chosen, the time of day, the type of shift, and intraindividual differences. Moreover, a process evaluation will be performed in order to gain more insight into what aspects of the intervention work for whom and why [48]. The process evaluation outcomes are assessed qualitatively (ie, group interviews, observations, data logs) and quantitatively (ie, self-reported measures in digital surveys) and whenever possible, complemented with objective organizational data (eg, sickness absence registration).

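### The EMA comparison of relaxation with activation concerns a self-chosen activity; before-after change, or after-break ratings, compared by activity type can show a difference where none exists

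*Protocol article*

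**What the plan says.** **The aim.** In the EMA section: "The information provided will give insight into the effectiveness of the different recovery strategies (eg, relaxation and activation"). The Study Strengths section goes further and says the EMA serves to "determine the influence of the type of recovery strategy chosen, the time of day, the type of shift, and intraindividual differences".

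**Who sets the activity.** The worker does. Study Objectives holds that either type of activity may work "as long as employees have a sense of control with regard to choosing their recovery activities". Table 1 measures this control at each break: "I was able to decide for myself how to spend my time during this work break". In Phase 1, "employees will be asked for their recovery needs (eg, preferred work break activities) in context to specific work shifts (ie, morning, evening, night"), so preferences are sought separately by shift.

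**How activity is recorded.** By self-report after the break: "1 item scored with 3 answering categories: 1 (on activation activities such as walking, exercising, playing a game"), with relaxation and other activities as the remaining categories.

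**The analysis.** The Statistical Analysis section names "multilevel analyses on data collected within the EMA study (before break-after break and before break-after shift comparisons"). The only confounder step described there compares person characteristics between the two units. Study Limitations discusses missing randomization only for intervention versus control group.

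**What is measured before the break.** Sleepiness, stress, shift type and the item "To what extent are you in need of a work break right now". Detachment and level of recovery are rated only after the break.

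**The concern.** A freely chosen exposure is not comparable across breaks, even within one person. Suppose a worker tends to sit or nap when sleepier than usual and to walk when more alert. Relaxation breaks then start from a worse state. Momentary sleepiness tends to return towards the person's usual level whatever is done, so relaxation shows the larger before-after improvement. On the after-break rating taken alone the bias has the opposite sign, because part of the worse starting state is still present. The same data could therefore favour relaxation on one summary and activation on another when the two are equal.

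A multilevel model with a person effect removes stable differences between workers. It does not remove this bias, which arises between breaks of the same worker.

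At stake is the credibility of any statement from the EMA about which type of break activity helps more.

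**Working it through.** **The plan's own figures.** The article gives none for the activity comparison. Its sample size (37 per group) is for the survey. It reproduces as a group-by-time interaction with Cohen f = 0.15 if three time points and a correlation of 0.5 are assumed: N = 73, so 37 per group, with power 0.806 at 74. It has no bearing here, except that the expected respondents (150 × 0.75 / 2 = 56.25, stated as 56 per group) suggest about 112 workers.

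**Assumptions, since the documents give no values.** Within-person SD of pre-break sleepiness s = 1.5 points; between-person SD 1.0; within-person pre-post correlation r = 0.3, 0.5 or 0.7; 8 reported breaks per worker; the log-odds of choosing relaxation rise by b per SD of momentary sleepiness; both activities have the same true effect. Odds ratios of 1.28 and 1.65 correspond to b = 0.25 and 0.5. They move the chance of relaxing from 50% at the usual state to 1.28/2.28 = 56% and 1.65/2.65 = 62% at one SD sleepier.

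**Approximate formulas.** With the two activities about equally common and b small:

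- pre-break gap, relaxation minus activation ≈ b × s
- false difference in before-after change ≈ −(1 − r) × b × s
- false difference in after-break rating ≈ + r × b × s

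For r = 0.5:

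- b = 0.25: change −0.5 × 0.25 × 1.5 = −0.19; after-break +0.19
- b = 0.5: change −0.5 × 0.5 × 1.5 = −0.38; after-break +0.38

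**Simulation.** 1,000 runs per cell, true difference zero, within-person estimate, two-sided 0.05. Each entry is the false difference in change (points), followed by the rejection rate.

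| Odds ratio per SD | r = 0.3 | r = 0.5 | r = 0.7 |
|---|---|---|---|
| 1 (choice unrelated to state) | 0.00; 4.0% | 0.00; 4.7% | 0.00; 4.8% |
| 1.28 | −0.26; 54% | −0.18; 40% | −0.11; 28% |
| 1.65 | −0.49; 97% | −0.35; 91% | −0.21; 74% |
| 2.72 | −0.87; 100% | −0.62; 100% | −0.37; 99.7% |

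The formula agrees closely at small b and slightly overstates at larger b, as expected of a linear approximation. If sleepier workers chose activation instead, the signs would reverse and the sizes would stay the same.

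**With adjustment.** Adding the same break's pre-break score as a within-person covariate brings the difference to about 0 and the rejection rate to 4% to 6% in every cell of the table.

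**Limit of the adjustment.** One run added an unmeasured momentary factor that affects both choice and outcome (b = 0.5, r = 0.5). The adjusted estimate was +0.24 with 65% rejection. The unadjusted change estimate in that run was −0.11 with 16% rejection, because two biases of opposite sign partly cancelled. Adjustment removes the part due to the measured state and leaves the rest.

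**The case against.** Several objections are fair.

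- **The contrast is not tied to activity type.** The Statistical Analysis section attaches the before-after comparisons to the effectiveness of the intervention. A reader might infer that the plan commits to comparing raw change between relaxation and activation breaks. It does not say so, and multilevel analysis is compatible with the model proposed below. What stands is that an effectiveness aim for activity type is stated, and before-after comparison is the only EMA contrast offered to serve it.
- **A detailed analysis plan is promised.** The lack of a covariate list in an article is therefore no fault, and none is claimed. The point is an effectiveness statement about a self-chosen activity, with no caveat on self-selection at the break.
- **State-dependent choice is inferred.** A reader might take it as documented that workers choose by how they feel. The documents establish autonomy, and seeking preferences by shift makes dependence plausible, but neither its existence nor its direction is shown. The Introduction cites activity as a way to raise alertness, so sleepy workers might choose activation.
- **Pre-break information is not wholly unused.** The EMA section names shift type, work break control and personal characteristics as influences to be studied, and Study Strengths adds time of day. No use is stated for pre-break sleepiness, stress or need for a break as adjustment in the activity comparison.
- **The first research question does not hang on this.** A reader might infer that it does. The intervention is arrived at through user sessions, ratings, voting and a prototype with at least three practices, and a process evaluation and a comparison of the units' solutions are also planned. The EMA is described as showing working mechanisms.

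**Conclusion.** The point holds as a conditional one. If the choice of activity depends even modestly on the worker's state before the break, comparing before-after change or after-break ratings between activity types can show a difference between equal activities. With within-person SD 1.5, correlation 0.3 to 0.7 and odds ratio 1.28 to 1.65 per SD, the false difference in sleepiness change is about 0.1 to 0.5 points on the ten-point scale, and the false-positive rate is 28% to 97% with 112 workers and 8 breaks each. Stronger selection gives more. With no dependence the bias is zero and the error rate stays near 5%. All these inputs are assumptions. The calculation is for sleepiness; detachment and level of recovery were not simulated, and for them only the after-break mechanism applies.

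It would go too far to conclude that the EMA ranking will be wrong, or that adjustment would make it causal. The documents do not show how choice depends on state, and unmeasured momentary factors would remain.

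**What to change.** In the EMA analysis, for the activity-type comparison only:

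1. Use the after-break (or after-shift) rating as the outcome, with the same break's pre-break sleepiness, stress, need for a break and shift type as covariates, and activity centred on the person's mean. Use this instead of comparing raw before-after change between activity types.
2. Describe the result as a within-person association for self-chosen breaks, and align the wording in the EMA and Study Strengths sections with that.
3. Add residual confounding by unmeasured momentary factors to the limitations, stating that adjustment addresses the measured pre-break state and does not guarantee that the bias is gone.

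The cost is analysis and reporting text. Every variable is already in Table 1, and data collection does not change.

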#### Process Evaluation

It is not only important to develop an intervention with the right ingredients but also to design a good implementation process [48]. Studies have shown that the intervention development and implementation process can affect the outcomes of the respective intervention [27,28]. For instance, activities aimed at raising support from the employees and the management for the intervention may enhance the effectiveness of an intervention. However, failing to fully implement a planned intervention after raising support may result in unfulfilled expectations and negative employee attitudes. By evaluating the intervention process, the outcomes of organizational interventions can be better understood [48,49]. These insights can be used to further improve the intervention effectiveness.

In this study, we will use Nielsen and Randall’s [50] framework for process evaluations, which is specifically designed for the implementation process of organization-level interventions. It provides a broad perspective on the intervention process by not only including the intervention design and implementation but also the organizational context and the participant’s perceptions of the intervention. Evaluation of these factors will enable us to answer the questions of what works for whom under which circumstances [48]. Data on the process factors will be collected during and after the implementation of the intervention. A variety of data sources will be used: (1) data logs of the researchers and the organizational management, (2) interviews with the management and the employees, and (3) the T1/T2 web-based employee survey. Table 2 provides an overview of the process factors, associated questions, and data sources.

**Table 2 table2:** Overview of the process evaluation factors.

Process factor		Question	Data logs	Interviews	T1/T2^a^ survey
**Intervention design and implementation**					
	Initiation	Who initiated the intervention and for what purpose?	✓	✓	
	Developing intervention activities	Did the intervention activities target the problems of the workplace?	✓	✓	✓
	Implementing intervention activities	Did the intervention reach the target group?	✓	✓	✓
**Implementation strategy**					
	Drivers of change and the roles of key stakeholders	Who were/are the drivers of change?	✓	✓	
	Employee involvement	Did employees participate significantly in decision making and how many were involved?	✓	✓	✓
	Management support	What was the role of the senior/middle managers?	✓	✓	✓
	External consultants	What was the role of the external consultants? *(Not Applicable)*			
	Information and communication	What kind of information was provided to the participants during the study?	✓	✓	✓
**Context**					
	Omnibus context	How did the intervention ﬁt in with the culture and the conditions of the intervention group?	✓	✓	✓
	Discrete context	Which events took place during the intervention phase?	✓	✓	
**Mental models**					
	Readiness for change	To what extent are/were the participants ready for change?		✓	✓
	Shared mental models	To what degree do the participants have shared mental models?		✓	✓
	Appraisal of the intervention and its activities	How did the participants perceive the intervention and its activities?		✓	✓
	Changes in mental models	Did the intervention bring about a change in the participants’ mental models?		✓	✓

^a^T1/T2: Posttest web-based survey.

### Statistical Analysis

First, intervention results will be analyzed by performing mixed model repeated measures analyses (multivariate analysis of variance; time*group interaction) on longitudinal survey data with the outcome measures at follow-up (T0-T1, T1-T2, and T0-T2 comparisons) as the dependent variables. Furthermore, the effectiveness of the intervention will be analyzed by applying multilevel analyses on data collected within the EMA study (before break-after break and before break-after shift comparisons). Data will be collected and analyzed at 3 levels: (1) day level, (2) employee level, and (3) work unit level. Dropouts will be documented and included in the data analysis to the point of dropout. Potential confounders or effect modifiers (eg, age, gender, chronotype) will be compared between the intervention and the waiting list control group by *t* tests for independent samples and chi-square tests. For all analyses, a two-tailed significance level of *P*<.05 will be applied. The multilevel analyses will be conducted using R and the mixed model repeated measures analyses will be performed using SPSS software (IBM Corp, Version 25.0). A detailed analysis plan will be developed prior to finalization of the dataset.

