**Methods:**

This study is performed in 2 department units with shift workers at a multinational company in the steel industry. For each department, an intervention will be developed and implemented through an iterative process of user-centered design and evaluation. This approach consists of various sessions in which employees and a project group (ie, researchers, line managers, human resource managers, and occupational health experts) provide input on the intervention content and implementation. Intervention effects will be evaluated using pretest and posttest web-based surveys. Digital ecological momentary assessment will be performed to gain insight into the link between the intervention and daily within-person processes. The intervention process and participants’ perception of the interventions will be assessed through a process evaluation. Intervention results will be analyzed by performing mixed model repeated measures analyses and multilevel analyses.

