### Sample Size

The sample size calculation is based on finding an effect on the need for recovery. This variable was chosen because of its test-retest reliability and sensitivity to detect change, indicating that the need for recovery may be a useful tool for evaluating interventions related to occupational health [34]. Based on previous studies [47,51], a small effect size is expected. Power calculations indicate that to detect a small effect in the context of a repeated measurements analysis of variance (Cohen *f*=0.15), at least 37 subjects are necessary in each study group (power=0.80 and α=.05), and calculations were performed using G*power [52]. The response rates of similar PAR studies have been shown to be around 75% or higher [31,32]. Given the intended sample size of 150 subjects and the expected response rate of 75%, resulting in 56 subjects per group, the study has sufficient power to even detect slightly smaller effects [53].

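### The survey analysis is labelled both a mixed model and a MANOVA; these treat missing waves differently, and only the likelihood-based mixed model fits the dropout rule

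*Protocol article*

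**What the plan says.** All places are in the protocol article.

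- **Statistical Analysis, method:** the survey outcomes are to be analysed by "mixed model repeated measures analyses (multivariate analysis of variance; time*group interaction", with the outcomes at follow-up ("T0-T1, T1-T2, and T0-T2 comparisons) as the dependent variables").
- **Statistical Analysis, dropouts:** "Dropouts will be documented and included in the data analysis to the point of dropout". The sentence follows those on the ecological momentary assessment (EMA) data and the three data levels. It does not say whether it covers the survey, the EMA data or both.
- **Statistical Analysis, software:** "the mixed model repeated measures analyses will be performed using SPSS software (IBM Corp, Version 25.0", with no procedure named. The multilevel analyses of the EMA data are assigned to R.
- **Abstract, Methods:** "Intervention results will be analyzed by performing mixed model repeated measures analyses and multilevel analyses", with no mention of MANOVA.
- **Sample Size:** 37 per group for Cohen f = 0.15, "in the context of a repeated measurements analysis of variance", with 56 per group expected from 150 employees at a 75% response rate. No loss between waves is given.
- **Statistical Analysis, later detail:** "A detailed analysis plan will be developed prior to finalization of the dataset".

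**The concern.** The method sentence puts two different procedures under one name. A repeated-measures MANOVA works on one row per person and drops the row if any wave in the analysis is missing. A likelihood-based linear mixed model works on one row per person and wave and uses every wave that was answered. Only the second can keep a person's data up to the moment they leave.

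An analyst could follow the bracket in good faith. It is the only specification attached to the method. The paragraph separates this analysis from the multilevel models, as if it were another technique. The sample size is framed as a repeated-measures ANOVA. The word mixed may therefore mean a mixed-design (between-within) ANOVA.

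At stake are bias and precision. Under the Study Procedure section, participation is voluntary and people may stop without giving a reason. A completers analysis of fatigue and need for recovery is unbiased in general only if loss is completely at random. A mixed model needs the weaker condition that loss depends only on what has been observed, for instance the T0 score.

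**Working it through.** **1. The plan's own sample size.** Inputs from the Sample Size section: f = 0.15, power 0.80, α = 0.05. Assumed, because not stated: correlation between waves ρ = 0.5 and sphericity ε = 1. For two groups (k = 2), three waves (m = 3) and the within-between interaction:

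- λ = f²·N·m/(1 − ρ) = 0.0225 × 74 × 3/0.5 = 9.99
- df1 = (k − 1)(m − 1) = 2; df2 = (N − k)(m − 1) = 72 × 2 = 144
- power = 0.806 at N = 74, the smallest even total to reach 0.80

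This gives 37 per group, as stated. (The main effect of time gives the same figure.) The multivariate form needs 38 per group and has power 0.797 at N = 74. Two waves would need 45 per group. So 37 fits a three-wave ANOVA in which each counted person has all three waves.

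**2. Expected starting number.** 150 × 0.75/2 = 56.25, so 56 per unit, as stated.

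**3. Complete cases if the MANOVA or ANOVA label is followed.** Let d be the loss at each follow-up wave, which is an assumption. With independent losses, complete cases per unit are 56(1 − d)². If the same people miss both waves, they are 56(1 − d). Power is computed as in step 1, with the independent-loss count rounded down.

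| Loss per wave | Complete, independent loss | Power ANOVA / MANOVA | Complete, same people miss both |
|---|---|---|---|
| 10% | 45.4 | 0.88 / 0.88 | 50.4 |
| 15% | 40.5 | 0.84 / 0.83 | 47.6 |
| 20% | 35.8 | 0.78 / 0.77 | 44.8 |
| 25% | 31.5 | 0.73 / 0.72 | 42.0 |
| 30% | 27.4 | 0.66 / 0.65 | 39.2 |

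The count reaches 37 when d = 1 − √(37/56) = 0.19 under independence. If the same people miss both waves, it does so at d = 1 − 37/56 = 0.34.

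**4. If the comparisons are run in pairs.** Someone missing only T2 stays in T0-T1, and someone missing only T1 stays in T0-T2. Someone with T0 only is in none. Under the Quasi-Experimental Field Study section, unit B waits a further 3 months, so T0-T1 is the only comparison with an untreated control. At 20% loss at T1 it keeps 56 × 0.80 = 44.8 per unit, against the 45 that a two-wave design needs (power 0.795 at 44).

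**5. Records kept by each method.** In one simulated data set of 112 people with 20% loss at each follow-up wave, a mixed model used all 276 records from 112 people. Listwise deletion kept 74 people over three waves and 90 for T0-T1.

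**The case against.** The strongest reply is that the plan names a mixed model. MANOVA appears once, in a bracket, while the Abstract and the software sentence speak of a mixed model without it. Read that way, the dropout rule can be followed. This stands: a reader might infer that the analysis is definitely a MANOVA and that the two sentences cannot both be honoured, and the text does not support that.

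Four further points limit the concern.

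- **Not everyone with a gap is lost.** A reader might infer that every participant with a missing wave is dropped. Under pairwise comparisons that is not so (step 4).
- **Scope of the dropout rule.** It may have been written for the EMA data. But it carries no such restriction, and if it excludes the survey, the survey is left without a stated rule.
- **Selective loss is not documented.** A reader might take the absence of follow-up of nonparticipants as evidence of it. In the Study Procedure section that remark concerns employees who decline consent at baseline. They are in no analysis under either method.
- **Power.** The wave losses are assumed. Independence is the unfavourable case, and 25% is a further loss after the 75% response has already been applied. Powering on an ANOVA is also a common approximation for a later mixed model and does not prove that an ANOVA will be run.

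The promised analysis plan can supply the detail. It does not remove the conflict, because the label and the dropout rule are already stated here and the later plan would inherit both.

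**Conclusion.** The point holds as a conflict of labels. The Statistical Analysis section equates two methods that treat missing waves differently, and only the likelihood-based mixed model is compatible with including dropouts up to when they leave. If the other label is followed, the survey result is a completers analysis, open to bias unless loss is completely at random.

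The size depends on between-wave loss, which the article does not give. With independent losses of 10%, 20% or 25% per follow-up wave, 56 per unit becomes about 45, 36 or 32. The stated minimum of 37 is missed from about 19% per wave. Up to 15% the power cost is modest (at least 0.83), and if the same people miss both waves the number stays above 37 until about 34%. A reader might infer that the study is underpowered; the documents do not show that. The power figures rest on ρ = 0.5 and ε = 1. The possible bias does not depend on those values and remains at low loss. The change should be made, since it costs almost nothing.

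**What to change.** In the Statistical Analysis section:

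1. Delete the reference to multivariate analysis of variance.
2. State that the survey outcomes are analysed with a likelihood-based linear mixed model (for example SPSS MIXED) with wave, unit and wave-by-unit terms, using all available waves of every participant.
3. Take the T0-T1 contrast between units from that model.
4. State that the dropout sentence covers the survey data.

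The covariance structure and estimation details can be left to the analysis plan. The cost is a few words, before the dataset is finalised. SPSS is already the named software, and no data collection changes.
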